#### Recruitment

Subjects will be recruited from diabetes and sleep clinics at KUMC, university advertisements, community centers in Kansas City, flyers, personal referrals and newsletters, and a registry of patients from KUMC who have signed up to be contacted about potential research opportunities.

### Assignment of Interventions (for Controlled Trials)

#### Allocation Sequence Generation

We will use random mixed block size randomization [125] to assign participants to either CBT-I (n=14) or HE (n=14) groups. Participants will be stratified by age where 62 years is the value that will stratify participants into either the older (63-75 years) or the younger (40-62 years) age group. The reason we chose age as a blocking variable is that the impact of age on sleep is more pronounced than gender [126], as older adults often have poorer [127] and lower slow wave [128] sleep, as compared with young adults.

#### Allocation Concealment Mechanism

Participant allocations will be placed in sealed envelopes. The envelopes are prepared by a research assistant, who withholds this information from the CBT-I provider. After finishing the baseline assessment, participants will be asked to open the sealed envelope to disclose their group allocation. Microsoft Excel will be used to create the randomization lists.

#### Allocation Implementation

A computer will be used to generate the random mixed block size randomization sequences. Results of the generator will be concealed from the assessor and CBT-I provider. Participants will be asked to open the sealed enveloped after informed consent and baseline assessment are completed.

#### Blinding

The assessor, who is blinded to group allocation, will score the Actigraph data. The assessor will have experience in scoring criteria and no involvement in providing the interventions. The CBT-I provider will not be blinded in this study.

#### Data Collection, Management, and Analysis

##### Data Collection and Methods

Insomnia severity (primary outcome); sleep variability; fatigue; DSCB; A_1c_; daytime sleepiness; sleep quality; glucose levels; and symptoms of depression, anxiety, and pain will be measured a week before and after the intervention.

##### Data Management

All study-related procedure will be performed at Georgia Holland laboratory in Hemenway Life Sciences Innovation Center on the KUMC campus. All obtained participant records will be kept in locked cabinet inside the Georgia Holland laboratory. Electronic study data will be saved in the KUMC Research Electronic Data Capture system. For voice records, all tapes will be saved on a secure university-supported network drive.

##### Statistical Methods

A chi-square test will be used to compare between-group differences in categorical variables. Independent 2-sample *t* tests will be used to compare differences in continuous between-group demographic characteristics and clinical variables.

For the main analysis**,** the effect of the CBT-I intervention will be investigated by calculating change scores for the insomnia severity; DSCB; A_1c_; fatigue; sleep quality; daytime sleepiness; and symptoms of depression, anxiety, and pain. In addition, for variability of each sleep outcomes (SE, SL, TST, and WASO), CV of 7 nights before the pre- and postintervention assessments will be calculated, and change scores will be calculated. Then, independent sample *t* tests will be utilized to investigate the between-group difference in the change score means of all outcomes. A completer vs noncompleter analysis will be performed. For all analyses, alpha level will be set at .05.

Owing to the complex relationship between insomnia and T2D, some factors are needed to be controlled to fully investigate the relationship. Owing to the small sample size and possible covariates that might not be included in the power calculation, these complex relationships will be investigated using exploratory analyses. Post hoc analysis using the type and number of medications will used to address the potential confounding effects on the outcomes. Univariate linear regression will be used to control for demographic and clinical variables (covariates). The decision to perform these analyses with demographic and clinical variables will be made if there are significant between-group differences at baseline in depression symptoms, anxiety symptoms, pain symptoms, gender, diabetes duration, or body mass index. Mixed models will be used to account for the correlation between times in pre- and posttest (7 nights as random factor) sleep variability (as dependent variable) and facilitate adjustment for covariates to compare the difference in sleep variability between the CBT-I and HE groups (groups as fixed factor). Covariates will be determined if there is a difference in the baseline assessment for demographic and clinical outcomes. Those participants who are treated with CPAP will be asked to report their compliance using CPAP during baseline and postintervention assessments. Subjects who are using VPAP will be given a modified sleep diary to check off nights of CPAP compliance during the assessment sessions. An exploratory subanalysis will be utilized to investigate the difference in insomnia severity between compliance and noncompliance with CPAP. Noncompliance is defined as (1) missing more than 2 nights during the 7 nights period that the participant is wearing the Actigraph or (2) using the CPAP for <4 hours per night during this study.

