**Methods:**

This RCT will use random mixed block size randomization with stratification to assign 28 participants with T2D and insomnia symptoms to either a CBT-I group or a health education group. Outcomes including insomnia severity; sleep variability; diabetes self-care behavior (DSCB); glycemic control (A_1c_); glucose level; sleep quality; daytime sleepiness; and symptoms of depression, anxiety, and pain will be gathered before and after the 6-week intervention. Chi-square and independent *t* tests will be used to test for between-group differences at baseline. Independent *t* tests will be used to examine the effect of the CBT-I intervention on change score means for insomnia severity, sleep variability, DSCB, A_1c_, fatigue, sleep quality, daytime sleepiness, and severity of depression, anxiety, and pain. For all analyses, alpha level will be set at .05.

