## Methods

### Trial Design

The study design will be a pilot randomized controlled trial (RCT). This study will have an allocation ratio of 1:1, and this pilot RCT will be using a superiority framework to test the effectiveness of the experimental CBT-I intervention. This protocol is in accord with the Standard Protocol Items: Recommendations for Interventional Trials 2013 statement [65], and the intervention will be described according to the Consolidated Standards of Reporting Trials 2010 guideline [66].

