#### Sample Size

To detect the effect of CBT-I on people with T2D and symptoms of insomnia, the change in pre-post ISI was used to determine sample size. Pre-post changes using the minimal clinically meaningful difference of 8 points for the ISI in a previous study [124] were used to estimate the effect size. This calculation resulted in 10 participants per group to reject the null hypothesis of equal means when the population mean difference equals 8 with a standard deviation of 7. We accounted for an expected attrition rate of 40%, which indicated 28 subjects in both groups to detect the significant difference between groups after allowing for attrition at a .05 significant level and power of .80.

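### The primary ISI comparison fixes the baseline slope at 1 and leaves out the age stratum; a prespecified ANCOVA would be a modest, nearly cost-free improvement

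*Protocol article*

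**What the plan says.** The Statistical Methods section of the protocol article fixes the main analysis. Change scores are computed, and independent-sample t "tests will be utilized to investigate the between-group difference in the change score means of all outcomes". The abstract says the same for the primary outcome: t "tests will be used to examine the effect of the CBT-I intervention on change score means for insomnia severity". No covariate is named, and "For all analyses, alpha level will be set at .05".

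The section on allocation sequence generation states: "Participants will be stratified by age where 62 years is the value that will stratify participants" into a 40-62 and a 63-75 year group. The reason given is that age affects sleep more than gender does.

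The rest of Statistical Methods places adjustment among exploratory analyses and cites the small sample. Regression adjustment is used only if the arms differ significantly at baseline in depression, anxiety, pain, gender, diabetes duration or body mass index. Baseline ISI and age are not on that list. The mixed models with covariates concern sleep variability, not ISI.

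The Sample Size section says that "the change in pre-post ISI was used to determine sample size".

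**The concern.** A t test on change scores assumes that each extra baseline point predicts exactly one extra post-treatment point. If the true slope b is below 1, the arm that starts higher by chance tends to fall further whatever the treatment does. Part of that chance difference then appears in the treatment estimate. With 14 per arm at most, such imbalances are not rare, and many will not reach significance in a baseline test. The planned trigger would therefore miss them even if baseline ISI were on the list.

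The protocol also treats age as important enough to stratify on, then leaves the stratum out of the analysis. To the extent that age predicts change in ISI, this leaves explainable variation in the error term.

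What is at stake is the precision of the primary result, and its credibility if the arms happen to start apart. The validity of the test is not at stake.

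**Working it through.** **Inputs.** From Sample Size: "the population mean difference equals 8 with a standard deviation of 7", and "at a .05 significant level and power of .80"; 10 per group; 40% attrition; 28 in total. From Trial Design: 1:1 allocation, and "this pilot RCT will be using a superiority framework", with sidedness not stated. Not in the article, so assumed: the correlation r between baseline and post-treatment ISI, and the ratio k of post-treatment SD to baseline SD. SD 7 is read as the SD of change, because the calculation is framed on pre-post change.

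**The plan's own figure.** The one-sided normal formula gives n = 2 × [7 × (1.645 + 0.842)/8]² = 9.47, so 10 per group, as stated. The two-sided normal formula gives 12.02, so 13; the two-sided t test needs 14. The total follows as 20 × 1.4 = 28. At 40% attrition, 28 × 0.6 = 16.8 complete, about 8 per arm.

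**Power of the planned test** (noncentral t, two-sided .05, difference 8, SD 7): 57% at 8 per arm, 68% at 10, 83% at 14.

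**What adjustment changes.** Within arms, Var(change) = Var(ANCOVA residual) + (1 − b)² × Var(baseline). In terms of r and k:

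variance ratio = k²(1 − r²) / (1 + k² − 2rk), which equals (1 + r)/2 when k = 1.

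- k = 1: 0.65 at r = 0.3; 0.80 at r = 0.6; 0.90 at r = 0.8.
- k = 1.5: 2.0475/2.35 = 0.87 at r = 0.3; 1.44/1.45 = 0.99 at r = 0.6.

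**Power with ANCOVA.** These values come from simulating the full model (arm, baseline ISI, balanced age stratum with no effect of its own). They therefore include the two degrees of freedom and the cost of estimating the slope, and are good to about one percentage point.

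| | 8 per arm | 10 per arm | 14 per arm |
|---|---|---|---|
| Change-score t test | 57% | 68% | 83% |
| ANCOVA, k = 1, r = 0.3 | 71% | 83% | 94% |
| ANCOVA, k = 1, r = 0.6 | 61% | 75% | 89% |
| ANCOVA, k = 1, r = 0.8 | 56% | 69% | 85% |
| ANCOVA, k = 1.5, r = 0.3 | 58% | 70% | 86% |
| ANCOVA, k = 1.5, r = 0.6 | 53% | 65% | 81% |

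**Effect of the ISI >10 entry rule.** Take r = 0.5 and equal SDs before selection (variance 1 each), with a cut at the mean. The slope stays 0.5 and the residual variance stays 0.75, but Var(baseline) falls to 1 − 2/π = 0.363. Then Var(change) = 0.75 + 0.25 × 0.363 = 0.841, and the ratio is 0.75/0.841 = 0.89, an 11% reduction in variance. Without selection it is 0.75/(0.75 + 0.25) = 0.75, a 25% reduction. After selection r is about 0.33 and k = √(0.841/0.363) = 1.52. Selection on baseline therefore moves the trial towards the k = 1.5 rows and shrinks the advantage.

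**Chance imbalance.** Given a baseline difference D between arms, the change-score estimate is shifted by (b − 1) × D. The standard deviation of D is √(2/n) baseline SDs: 0.38 at 14 per arm and 0.50 at 8. For illustration, assume a baseline SD of 5 and b = 0.5. A one-standard-deviation imbalance then shifts the estimate by about 0.5 × 1.9 = 0.9 ISI points at 14 per arm, and 0.5 × 2.5 = 1.25 points at 8, against a target of 8.

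**The case against.** The case for leaving the plan alone is substantial. Design and analysis agree: the trial is sized on change in ISI and tests change in ISI. Under randomisation the test is unbiased and controls type I error, and a change score does take baseline into account by subtracting it. The protocol gives a reason, its small sample, for keeping adjustment exploratory. Age is linked in the text to level of sleep, not to change in ISI, and a stable level effect cancels in a change score. Omitting a prognostic stratum makes the test conservative, not invalid. In about 16 people, estimating a slope costs something, and the table shows cases where ANCOVA does no better or slightly worse.

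All of this stands, and it rules out three stronger readings that a reader might infer:

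- That the t test is biased or that ANCOVA removes bias. The shift is conditional on the baseline imbalance that happens to occur; it averages to zero over randomisations.
- That ANCOVA would make good most of the power shortfall. That needs a low r and equal SDs, and the article gives neither.
- That the ISI >10 cutoff makes change scores perform especially badly. Selection on baseline lowers r, but it also reduces baseline variance, and the net effect is a smaller advantage for ANCOVA.

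The power shortfall itself is a sample-size matter. It depends on a two-sided test and on the full 40% attrition; with 14 completers per arm the planned test has 83% power.

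The objection does not defend the trigger rule. Making adjustment depend on baseline significance tests, with baseline ISI and age off the list, gives no protection against imbalance in the covariate most directly tied to the primary outcome.

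**Conclusion.** The point holds as a modest improvement in precision and in robustness to chance baseline imbalance. The primary analysis is valid, but it assumes a baseline slope that could be estimated, and it leaves out the one factor on which randomisation was stratified.

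The size is uncertain. With SD of change 7, a two-sided test, equal SDs and no credit for age, the change in power runs from about +14 points (r = 0.3) to about −1 (r = 0.8) at 8 per arm, and from about +15 to +1 at 10 per arm. If the post-treatment SD exceeds the baseline SD, which the entry cutoff makes likely, the gain is small or nil, and a loss of a few points is possible at 8 to 10 per arm. Any benefit from the age stratum cannot be quantified from the article.

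**What to change.** Name as the primary analysis an ANCOVA of post-intervention ISI on arm, baseline ISI and age stratum (40-62 / 63-75). Prespecify it, so that it is not triggered by baseline tests. Report the adjusted difference with its 95% confidence interval, and keep the change-score t test as a sensitivity analysis. Use the same form, with each outcome's own baseline value and the age stratum, for the other outcomes now assigned to change-score t tests.

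The Results section reports that recruitment is complete. The change should therefore be documented before any unblinded analysis; if that point has passed, the ANCOVA should be reported as post hoc.

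The cost is a change of wording and two degrees of freedom; the data are already collected. The downside to state openly is the possible loss of a few points of power at 8 to 10 completers per arm if the true slope is close to 1.

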### Participant Timeline

All measurements will be performed at baseline and 1 week after treatment completion (Figure 3). Participants who wish to withdraw during the intervention will be asked to complete the reassessment session.

At initial contact with a potential subject, a phone screening or diabetes clinic interview will be conducted by a member of the research team to determine whether an individual qualifies to progress to an in-person screening for the study. The phone screening interview assesses participant eligibility according to age, self-report of T2D diagnosis, insomnia severity, ability to understand English, STOP-Bang score, RLS Diagnostic Index, pregnancy status, alcohol use, night-shift work, and undiagnosed neurological disorders.

Individuals passing the phone screening will be scheduled for an in-person screening session to assess eligibility according to symptoms of pain, depression, and anxiety.

Subjects will undergo the consent process in a private room at KUMC before completing any of the in-person screening assessments. Individuals passing the in-person screening will then immediately begin baseline assessment.

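### The primary ISI test is an unadjusted, available-case change-score t test with 40% attrition expected, so it is biased if loss depends on baseline ISI differently in the two arms

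*Protocol article*

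**What the plan says.** All places are in the protocol article.

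- **Statistical Methods**, main analysis: "the effect of the CBT-I intervention will be investigated by calculating change scores for the insomnia severity" and the other outcomes, after which "independent sample *t* tests will be utilized to investigate the between-group difference in the change score means of all outcomes".
- **Statistical Methods**, on incomplete participation: "A completer vs noncompleter analysis will be performed". Completer is not defined, and the purpose of the comparison is not given.
- **Sample Size**: "We accounted for an expected attrition rate of 40%, which indicated 28 subjects in both groups", with the detectable difference described as holding "after allowing for attrition at a .05 significant level and power of .80".
- **Participant Timeline**: measurements are taken at baseline and once more, 1 week after treatment ends. "Participants who wish to withdraw during the intervention will be asked to complete the reassessment session".
- **Allocation Sequence Generation**: randomisation is stratified by age (40-62 and 63-75 years), 14 per arm.

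Baseline ISI and age stratum do not enter the primary test. The exploratory regression is triggered only by significant baseline differences in a listed set of variables (depression, anxiety, pain, gender, diabetes duration, body mass index). That list includes neither baseline ISI nor age. The mixed model in the same section is for sleep variability, not ISI.

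**The concern.** A change score needs both ISI values. With a single post-treatment visit, a participant who misses it contributes nothing to the primary comparison, and the plan expects substantial loss. The Sample Size section also treats those who leave as lost to the test, since it recruits extra participants to make up for them.

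The arms differ in burden. One receives sleep restriction, and the Harms section expects a temporary increase in sleepiness; the other receives health education. It is therefore plausible that severity at entry affects who stays differently in the two arms. If so, the participants analysed no longer have comparable baseline ISI between arms. A raw change score carries that imbalance into the estimated effect, because change is itself correlated with baseline. What is at stake is the trial's single powered result.

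**Working it through.** **1. The plan's own figures.** For a difference of 8 and SD 7 at alpha 0.05 and power 0.80, the normal approximation gives 10 per group only for a one-sided test (13 two-sided). The step from 20 to 28 is 20 × 1.4 = 28, whereas 20 / (1 − 0.4) = 33.3, or 34. Both are separate points. What matters here is that the inflation counts those who leave as absent from the test.

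**2. How many could be missing.** 28 × 0.6 = 16.8, so about 17 would be analysed and about 11 missing (about 8.4 analysed per arm). This is an upper limit on missing ISI, because some who withdraw may be reassessed.

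**3. Why an unadjusted change score is exposed.** Three inputs are assumptions that do not stand in the documents: baseline SD 4, post SD 7, correlation 0.3. They were chosen so that the SD of change is close to the planned 7:

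√(4² + 7² − 2 × 0.3 × 4 × 7) = √48.2 = 6.9.

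The slope of post on baseline is 0.3 × 7 / 4 = 0.525. Improvement (baseline minus post) therefore has slope 1 − 0.525 = 0.475 on baseline. If the participants still observed differ between arms by D points in mean baseline ISI, the change-score contrast is off by 0.475 × D. A bias of 0.7 needs D = 0.7 / 0.475 = 1.5 points, and a bias of 1.4 needs D = 1.4 / 0.475 = 2.9 points.

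**4. Simulation.** 14 per arm, true effect 8, about 40% loss, logistic dropout on baseline ISI, with the inputs of step 3:

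| Loss depends on | Change-score t test | Baseline-adjusted |
|---|---|---|
| baseline ISI, equally in both arms | 8.0 | about 8.0 |
| arm only (30% vs 50%) | 8.0 | about 8.0 |
| baseline ISI, CBT-I arm only | 7.3, or 8.7 with direction reversed | about 8.0 |
| baseline ISI, opposite directions in the two arms | 6.6, or 9.3 with direction reversed | about 8.0 |

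With a dropout log-odds of 1 per SD of baseline, a separate run gave 7.37 (CBT-I arm only) and 6.76 (opposite directions). With log-odds 2 in the CBT-I arm only it gave 7.08. The signs agree with step 3: losing the more severe CBT-I participants shrinks the estimate, and losing the less severe inflates it.

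**5. Size against noise.** The standard error in the simulation is about 3.5. As a check, 6.9 × √(2 / 8.4) = 3.4. A bias of 0.7 to 1.4 is thus 0.7 / 3.5 = 0.2 to 1.4 / 3.5 = 0.4 standard errors.

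**6. What adjustment does not cure.** Suppose, for illustration, that the 40% lost would have had half or none of an 8-point benefit. The effect in all randomised participants is then 0.6 × 8 + 0.4 × 4 = 6.4, or 0.6 × 8 + 0.4 × 0 = 4.8. If baseline ISI does not explain who is lost, the adjusted model still reports about 8, as the t test does. Only a sensitivity analysis that shifts the missing values shows this.

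**The case against.** The strongest reply is that much of this is inference from silence. The article does not restrict the primary test to treatment completers or reject analysis as randomised. The completer sentence announces an extra comparison and does not define the primary population. An analysis set and missing-data rules commonly sit in a full protocol or SAP, which is not shown. All of that stands.

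A reader might infer more than the article supports:

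- **That the main result is a completer comparison.** Someone who stops treatment but attends the reassessment has a change score and can enter the test. Having a post-treatment ISI and completing treatment are different things.
- **That 40% of ISI values will be missing.** For the same reason, 40% is an attrition assumption and not a forecast of missing outcomes.
- **That the t test is valid only if loss is unrelated to baseline ISI and to arm.** This is too strong. Loss related equally to baseline in both arms, or to arm alone, left the estimate at 8.0.
- **That the test must overstate the effect.** The bias from baseline-dependent loss runs in either direction.

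It is also fair that the bias is well below one standard error, that no passage gives a dropout pattern, and that the article itself says more research is needed to verify this 28-person pilot.

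What survives does not rest on an omission. The article names its primary method, and that method ignores baseline ISI and the stratification factor and can use only those with a post ISI, while heavy attrition is planned for. A better method is available from the same data at almost no cost.

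**Conclusion.** The point holds in limited form. As written, the primary ISI analysis is an unadjusted, available-case change-score t test that may omit up to about 11 of 28 randomised participants. It is biased by about 0.7 to 1.4 points on a true effect of 8, in either direction, if loss depends on baseline ISI in one arm only or in opposite directions in the two arms.

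That size rests on the assumed baseline SD 4, post SD 7, correlation 0.3 and about 40% missing post ISI. It shrinks if withdrawers are reassessed or if the correlation brings the slope of post on baseline closer to 1. The documents do not show that such loss will occur. The 6.4 and 4.8 scenarios are illustrations of loss related to the unobserved outcome; they are not estimates of bias in this trial, and baseline adjustment would not remove them. The change is worth making because it is cheap.

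**What to change.** In Statistical Methods:

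1. Make the primary analysis a model of post-treatment ISI with arm, baseline ISI and age stratum (ANCOVA, or the equivalent constrained longitudinal model). In the simulation it was the baseline adjustment on the observed cases that removed the bias.
2. State that participants are analysed in their allocated arm and that the reassessment ISI of those who withdraw is included.
3. Define completer, and label the completer vs noncompleter comparison as descriptive or secondary.
4. Add one delta or tipping-point analysis, for example shifting missing CBT-I post ISI values by 0 to 8 points, because the adjusted model does not correct loss related to the unobserved outcome.

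The cost is wording and a little programming, with no new data or participants. In some dropout patterns the standard error is up to about 10% larger than for the t test. The Results section reports recruitment complete in September 2019, so the change should be dated and its timing relative to access to outcome data stated.

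### In the exploratory adjusted analyses, covariates are admitted by baseline differences between arms, so chance rather than prognostic value decides the model

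*Protocol article*

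**What the plan says.** All of this stands in the protocol article under Statistical Methods.

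- **Baseline comparison.** Arms are compared at baseline by chi-square and independent t tests ("A chi-square test will be used to compare between-group differences in categorical variables"), and "For all analyses, alpha level will be set at .05".
- **Main analysis.** This is unadjusted: independent-sample "tests will be utilized to investigate the between-group difference in the change score means of all outcomes".
- **Adjusted regression.** Because of the small sample, "these complex relationships will be investigated using exploratory analyses". Linear regression is to control for covariates, but only conditionally: "The decision to perform these analyses with demographic and clinical variables will be made if there are significant between-group differences at baseline". Six candidates are listed: BMI, duration of diabetes, gender, and the pain, anxiety and depression scores.
- **Mixed model for sleep variability.** In the same paragraph: "Covariates will be determined if there is a difference in the baseline assessment for demographic and clinical outcomes". This rule gives neither a list nor a threshold.

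Two other sections bear on the point. The Background names depression, anxiety, pain and obesity as risk factors shared by diabetes and insomnia that may worsen insomnia. Allocation Sequence Generation stratifies by age (40-62 and 63-75 years) because age affects sleep. Age is not among the six regression candidates, and neither is baseline ISI.

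**The concern.** The sequence is computer-generated and concealed, so a baseline difference between arms is a chance event. Its p-value carries no information on whether the variable predicts outcome, and it is prediction of outcome that makes adjustment worthwhile. A strong predictor with a moderate imbalance is left out, while an irrelevant variable with a large imbalance is put in.

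The article's own reasoning points the other way. It argues that certain factors need control because they relate to insomnia, which is a prognostic argument for fixing them in advance. It then lets an unrelated test decide entry.

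At stake are the precision of the adjusted estimates and the fact that the adjusted model cannot be known until the baseline tests have been run. In a trial of 28 people, chance imbalances are large, and readers will look to the adjusted results as a check on the main one.

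**Working it through.** The article states no figure for this rule, so there is none to reproduce.

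**Inputs from the article:** six candidates; alpha .05 (taken as two-sided, since sidedness is not stated); 14 per arm; difference 8 with SD 7, so an effect of 8/7 = 1.14 SD; expected attrition 40%. **Assumed:** the correlation between covariate and outcome, shown as a range.

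**1. How often the trigger fires.** Under randomisation each test is significant with probability about .05, whatever the covariate's prognostic value. For six independent tests, 1 − 0.95^6 = 0.265. Simulation with five continuous and one binary covariate gave 24-26%.

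**2. What imbalance is needed.** The threshold is t(.975, 26 df) × √(2/14) = 2.056 × 0.378 = 0.78 SD. At 10 per arm it is 0.94 SD.

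**3. What can pass unflagged.** An imbalance just under 0.78 SD in a covariate with correlation r shifts the unadjusted ISI difference by about 7 × r × 0.777 points. That is 1.6 points at r = 0.3, 2.7 at r = 0.5 and 3.8 at r = 0.7.

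**4. Precision at 14 per arm, in outcome SDs.** Unadjusted, the SD of the estimate is √(2/14) = 0.38. Always adjusting multiplies this by about √(1 − r²), with a small addition for estimating the slope. The simulated triggered model (six candidates, 8000 trials per scenario) is set beside it.

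| r | Unadjusted | Triggered | Always adjusted |
|---|---|---|---|
| 0.5 | 0.38 | 0.37-0.38 | 0.33 |
| 0.7 | 0.38 | 0.36 | 0.28 |

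At r = 0.7 the trigger recovers (0.38 − 0.36)/(0.38 − 0.28), about one fifth of the available gain. At r = 0.5 it recovers almost none.

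**5. Power for an effect of 8/7 SD, one covariate, 14 per arm (simulated).** The unadjusted t test has power 0.83.

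| r | Triggered | Always adjusted |
|---|---|---|
| 0 | 0.83 | 0.82 |
| 0.2 | 0.83 | 0.83 |
| 0.4 | 0.84 | 0.87-0.88 |
| 0.6 | 0.84 | 0.94-0.95 |

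After attrition, 14 × 0.6 = 8.4, say 8 per arm. At r = 0.2 the figures are then 0.56 triggered and 0.55 always adjusted, so there is no gain.

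**6. Type I error.** The triggered model rejects a true null in about 4-5% of trials and the fixed model in about 5%. The chance that either the unadjusted or the triggered result is significant under the null is 5.3-6.1%.

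**The case against.** The strongest reply is that the rule governs only analyses labelled exploratory, in a pilot, while the main comparison is fixed. That stands. A reader might infer that the ISI result itself is chosen by the trigger; it is not, because the change-score t test is specified unconditionally.

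Three other stronger readings also go too far:

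- **The 26% as a false-positive rate.** It is the chance of running at least one exploratory adjustment. The triggered test is, if anything, slightly conservative.
- **Univariate regression as one that cannot adjust.** The article does call the regression univariate, but the same sentence says it is meant to control for covariates. One dependent variable is therefore the natural meaning, and this is a query about wording only.
- **Age and baseline ISI as ignored.** Age is balanced by stratification and could enter the mixed model, whose rule has no list. Baseline ISI is part of the change score, although subtracting it is not the same as adjusting for it. Their absence concerns the regression list only.

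It is also fair to say that the trigger costs nothing against the planned t test (0.84 or 0.83 against 0.83). The loss is relative to what a fixed adjusted model could offer, and at low correlation that is nothing. None of this makes selection by baseline difference sound. It limits how much depends on it.

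**Conclusion.** The point holds for the exploratory adjusted analyses. Both entry rules select covariates on chance, and the mixed-model rule is the looser, having no list and no significance criterion. The article states these rules, so this is not detail left to an analysis plan.

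The harm is lost precision and a model not fixed in advance. It is not bias in the main analysis or excess type I error. At 14 per arm the power forgone runs from nil at a correlation of 0.2 or below to about 10 points at 0.6. With 8 per arm there is no gain from adjusting at 0.2 or below.

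The 26% assumes independent tests. The power figures assume normal data, a single prognostic covariate and a true effect of 8/7 SD. The change is worth making, but the main result does not depend on it.

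**What to change.** Delete the baseline-difference trigger for both the regression and the mixed model. For the adjusted analysis, name a fixed set: the baseline value of the outcome and the age stratum used in randomisation. Allow at most one further pre-named variable, such as baseline depression score, as a sensitivity analysis. State the regression as a linear model that includes arm and these covariates. Where the mixed model already carries the pre-test values as responses, the baseline is in the model and should not be entered again as a covariate.

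Timing matters. The article reports recruitment and study completion in September 2019, so the set is credible only if it is fixed and dated before outcomes are examined by arm. If they have already been examined, the adjusted analysis should be labelled post hoc.

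The cost is analysis wording; the data are already collected. Statistically it takes one or two degrees of freedom, with a slight loss of power if the covariates prove unrelated to outcome (about 0.82 against 0.83 at zero correlation for one covariate, 14 per arm).
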